### **2.2. Secondary Outcome Measures**

#### **Maternal strata**

- Maternal toxicity – score and grade (tolerability and safety)
- Bacterial load in neonates exposed to maternal antiseptic, compared to control
- Serious adverse events

#### **Neonatal strata**

- Adapted neonatal skin condition score (safety) (absolute score and grade)
- Temperature (change in absolute temperature and grade (hypothermia))
- Serious adverse events

### **2.3. Additional secondary efficacy outcomes not in protocol**

#### **Maternal strata**

- Change in vaginal and perineal bacterial load (in log CFU) of specific species:
  - All gram positive
  - All gram negative
  - Yeast
  - All enterobacterales combined (E. coli, Enterobacter, klebsiella, Proteus-Providencia-Morganella, Serratia, other enterobacterales)
  - Klebsiella spp.
  - E. coli
  - Serratia spp.
  - Proteus-Providencia-Morganella
  - Enterobacter spp.
  - Acinetobacter spp.
  - Staphylococcus aureus
  - Group A streptococcus (GAS)
  - Group B streptococcus (GBS)
  - GAS and GBS combined
  - Enterococcus spp.
  - Candida spp.
  - Pseudomonas spp.
  - Salmonella spp.

- Other Enterobacterales
- Acquisition and loss of specific species above
- Components of total CFU considered separately
- Components of skin scores considered separately

#### **Neonatal strata**

- Change in neonatal skin bacterial load (in log CFU) of specific species as per maternal strata
- Acquisition and loss of specific species as per maternal strata
- Components of total CFU considered separately
- Components of skin scores considered separately

## **2.4. Sample Size Calculation**

There is very little data on bacterial load in neonates in LMICs. Additionally, bacterial loads are expected to differ across locations complicating interpretation of previous studies. For example, previous studies in neonates have found varying effects of CHG on log colony counts: a decrease from baseline to 24h of 0.2 SD with 1% CHG in Nepal (2) and 2SDs with 2% CHG in the USA (3). The primary endpoints of log colony forming units (CFUs) are widely accepted to be normally distributed. Sample size calculations used standard formula with Bonferroni adjustment for multiple testing within arms of frequency and antiseptic. Within each stratum, 147 individuals randomized to 7 treatment groups, 21 participants per group, provides 90% power to detect a difference of 0.82 standard deviations (SDs) between antiseptics (two-sided  $\alpha=0.012$ ) and 0.58 SDs between frequencies ( $\alpha=0.05$ ) (80% power for 0.72 and 0.50 SDs, respectively). This also provides 90% power to detect a difference of 1.01 SD between each antiseptic and SOC ( $\alpha=0.012$ ), and 0.90 SD between frequency and SOC ( $\alpha=0.025$ ) (0.88 and 0.79 SDs at 80% power). These expected effects were judged by clinical and statistical members of the team to be sufficient for selecting a treatment regimen for a future trial.

## **2.5. Method of Randomisation**

Randomisation is performed using a random number generated as implemented in the statistical computing environment R. Randomisation is by permuted blocks (random block sizes of 7 and 14 randomly selected) to guard against bias introduced over time, such as outbreaks of pathogenic bacteria in the hospital. Participants are randomised 1:1:1:1:1:1 to the 6 treatment and 1 SOC arms.

Randomisation is built into electronic data systems using algorithms developed by the data management team at the Malawi Liverpool Wellcome Trust (MLW). The participant's trial number, treatment allocation and the date of randomisation is entered into the trial register at the site.

## **2.6. Estimands**

The intervention is the randomised antiseptic and frequency of application.

The patient population is labouring mothers and new-born babies, with birth weight over 1kg admitted to hospital, as defined by the inclusion and exclusion criteria.

The co-primary endpoints are change in skin bacterial colony load, taken from vaginal and perineal swabs in the maternal strata and neck and perirectal swabs in the neonatal strata.

The population-level summary which provides a basis for comparison between treatment conditions is the difference in mean log colony forming units adjusted for baseline value.

Anticipated intercurrent events and associated strategy are:

- Loss to follow-up: rates are unknown but may be high as not many women are anticipated to labour for 32h. The mixed model gives valid estimates assuming outcomes are missing at random.
- Deviation from randomised strategy (antiseptic application and frequency as per protocol) will be assessed using multiple sensitivity analyses:
  - sensitivity analysis will censor at deviation from randomised strategy. Estimated treatment effects will then correspond to the (hypothetical) setting of no deviation.
  - sensitivity analysis using (a) post-intercurrent event data where appropriate and (b) MI will be used to assess robustness of treatment effect inferences where rates of deviation from protocol are above 15%.
  - sensitivity analysis using Inverse-probability weighting methods to adjust for deviation from randomised strategy if deviation rates are above 15%.

## 2.7. COVID-19

Eligible patients will be mothers and neonates within the hospital so risk of COVID-19 will be low. NeoVT-AMR was designed before the COVID-19 pandemic and so there are no explicit statistical mitigation strategies. Rate of positive COVID tests in trial participants and any resulting changes to treatment will be monitored and addressed in the analysis if necessary.

## 2.8. Interim analyses

The DMC met around the time the trial started (without reviewing any data) to ensure they were familiar with its design and conduct. They formally reviewed data halfway through planned recruitment. They may call additional meetings at any time at their discretion. In addition, SARs are sent in real time during the trial to the DMC. The DMC can recommend premature closure or reporting of the trial, or that recruitment to any randomised group be discontinued or modified. Such recommendations would be made if, in the view of the DMC, there is an unacceptable rate of adverse reactions. There will be no early stopping for clinical efficacy because this pilot trial is powered only to detect differences in skin bacterial load, not clinical efficacy outcomes.

The review halfway through recruitment was held on 8th November 2022 and reviewed safety data but not efficacy, as per the protocol. The SAP was not signed off at this point as there were still some unresolved questions from the statistical and DMC reviewer around the analyses of the efficacy endpoints. It was agreed with the DMC that it was preferable to go ahead with an incomplete SAP than delay safety analyses. Note that there were no issues around analyses of the safety endpoints considered during the DMC. V0.5 was the version in use during the DMC review. A SOP deviation was completed for this.

There will be no adjustment to the significance level due to interim analysis.

## 2.9. Final analyses

Final analysis will be after database lock following last-patient last-visit.

## **2.10. Software**

Primary and secondary outcome analyses will be done in Stata v17 or later. Data preparation and analyses of other data will be done in R v4.2.1 or later.

### **3. Derivation of data to be analysed**

#### **3.1. Definition of baseline**

Baseline values for all measurements will be those recorded at screening either on the screening and enrolment form, or zero hour treatment and microbiology data from the treatment and microbiology forms.

#### **3.2. Follow-up timings**

Timings of swabs will be:

##### **Maternal strata**

- 0h (baseline)
- 4h
- 8h
- 24h
- 28h
- 32h

##### **Neonatal strata**

- 0 day (baseline)
- 1 day
- 2 day
- 3 day

#### **3.3. Loss to follow up**

Loss-to-follow up rates are unknown but may be high. Missing swabs will be monitored and participants may be replaced to maintain power. However, all baseline and post-baseline results will be included in analyses.

#### **3.4. Free text**

Free text fields in CRFs may be corrected for spelling and further categorised.

## 4. Statistical Analyses

Information will be presented in tables and may also be presented graphically to aid interpretation.

Recruitment data will be presented as per standard CONSORT diagrams (4). Baseline data tables will be presented overall. Unless stated, post-baseline data tables will be presented aggregated by antiseptic and by frequency (working days, alternate working days), with SOC presented separately. Variables will also be presented by factorial randomisation or arm if there is difference between randomised groups of  $p < 0.05$ , used as a flagging device for imbalance and expected for 1 in 20 characteristics by chance, with p-values from t-tests of differences between means for numeric variables and chi-squared tests or Fisher's exact test if cell values are small for categorical variables.

Statistical tests will use 95% confidence intervals unless otherwise stated. Associated two-sided p-values will be produced but binary conclusions of significant/not significant will not be drawn. As this is a pilot trial there will be no adjustment for multiple testing, although interpretation of results will take this into consideration.

All analyses will be included in the interim and final reports unless stated. All analyses will be presented by strata separately and not combined.

IQR: interquartile range

### 4.1. Recruitment & Randomisation

The following metrics will be presented by strata:

- Total randomisation, n(%)
- Randomisation to each antiseptic concentration: n(%)
- Randomisation to each application frequency: n(%)
- Randomisation to each antiseptic/freq combination: n(%)
- Eligibility: number and reasons for any participants randomised in error and excluded or ineligible children included in the analysis

### 4.2. Baseline

#### Maternal

- Age at randomisation (years): median (IQR)
- Estimated gestational age at labour: median (IQR)
- Gravidity: median (IQR)
- Parity: median (IQR)
- Antenatal care during pregnancy: n(%)
- Tuberculosis: n(%)
- HIV: n(%) positive, negative, unknown
- Gestational diabetes: n(%)
- Antibiotics during pregnancy: n(%)
- Antibiotics since admission: n(%)
- Cervical dilation at enrolment: median (IQR)
- Rupture of membranes at enrolment: n(%) yes, no

- If ruptured, how ruptured: n(%) spontaneous, assisted
- Prolonged rupture of membranes (>18h): n(%) yes, no, unknown
- Offensive liquor: n(%) yes, no, unknown

## Neonatal

- Prolonged rupture of membranes (>18h): n(%) yes, no, unknown
- Offensive liquor: n(%) yes, no, unknown
- Mother received antibiotics in labour: n(%) yes, no, unknown
- Mode of delivery: n(%) vaginal spontaneous, vaginal assisted, emergency caesarean section
- Maternal HIV status: n(%) positive, negative, unknown
- Age at enrolment (hours): median (IQR)
- Estimated gestational age at labour: median (IQR)
- Sex: n(%) male, female
- AGPAR Score at 1 minute: median (IQR)
- AGPAR Score at 5 minutes: median (IQR)
- AGPAR Score at 10 minutes: median (IQR)
- Where admitted: n(%) postnatal ward with mother, nursery HDU, nursery
- Reason for admission: n(%) routine for mum and baby, maternal complication – baby admitted with mum, birth asphyxia, other
- Any antibiotics prescribed before enrolment since birth: n(%)
- Chlorhexidine cord care given: n(%)

## 4.3. Non-Trial Treatment

### Maternal and neonatal strata

- Antibiotics received post-baseline: n(%)
- Other conmeds received post-baseline: n(%)
- Length of hospital stay: median (IQR)

## 4.4. Trial Treatment

The following metrics will be presented by factor and strata. Note that compliance to antiseptic will not be assessed as patients have individual dose bottles for application.

Note that swab timings are 0/4/8/24/28/32h in maternal strata and 0/1/2/3d in neonatal strata.

- Total number of antiseptic applications: median (IQR) and 1, 2... n(%)
- Timing of last antiseptic application: n(%) 0/4/8/24/28/32h in maternal strata and 0/1/2/3d in neonatal strata
- Number of antiseptic applications before each swab: median (IQR)
- Temperature taken before antiseptic application: n(%) in neonatal strata only
- Skin score assessed before antiseptic application: n(%)
- Temperature taken after antiseptic application: n(%) in neonatal strata only
- Skin score assessed after antiseptic application: n(%)

#### **4.5. Follow-up**

The following metrics will be presented by strata:

- Baseline swab: n(%) yes
- Number of swabs: median (IQR)
- Time in hours from baseline when each swab taken: median (IQR)
- Number of skin score assessments: median (IQR)
- Last time point of skin score assessment: : n(%) 0/4/8/24/28/32h in maternal strata and 0/1/2/3d in neonatal strata
- Day 28 follow-up: n(%)

#### 4.6. Primary outcome analyses

Note that no efficacy outcome data will be presented at the interim analysis. Analyses beyond the primary analysis may not be presented at final analysis, depending on results from primary analysis.

A summary table will be presented:

- Total log10 CFU at baseline: mean (SD) [N]
- Total log10 CFU at each assessment time point: mean (SD) [N]
- Change in total log10 CFU from baseline to each assessment time point: mean (SD) [N]

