#### **4.10.4. Analysis plan (brief)**

The analyses will be described in detail in a full Statistical Analysis Plan. This section summarises the main issues.

The primary analysis population is intention-to-treat, including all randomised participants, regardless of treatment received. This corresponds to estimating the impact of the effectiveness of the treatments. However, in secondary analyses we will also use inverse-probability weighting methods to adjust for deviation from randomised strategy, which is a more efficient approach than defining a per-protocol population.

Analysis of the co-primary endpoints will compare within-individual differences over time across randomised arm to maximise the information gained from the trial. Analysis will use linear mixed-models, with individual as a random effect, will adjust for baseline values of each outcome, and use Normally distributed errors. Analysis will be both frequentist, enabling straightforward comparison between arms (primary analysis since sample size is based on this), and Bayesian, enabling estimation of the probability that one arm is truly superior to another. This is more powerful when sample sizes are small as use of priors provides additional information. Sensitivity analysis to prior assumptions will be performed using optimistic, non-informative and sceptical priors.

The effect of each treatment arm will be assessed within a single model with each factor being fitted independently as a factor, and not as a continuous variable. Comparison of main effects within arms will be assessed using the estimate and 95% confidence interval of the comparison of differences between factors and in comparison, to control. As this is a pilot trial, the sample size was not powered to robustly detect interactions between treatment and frequency and so we will not test these formally, but will use exploratory analyses to assess whether there is any evidence supporting individual interactions testing each one, one at a time.

Similar mixed models will be used to analyse change in skin temperature after vs before each application, including individual as a random effect, the change in temperature as the outcome and the pre-application (baseline) temperature as a factor.

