**Interaction analysis**

- Interactions between antiseptic and frequency, antiseptic and timepoint of swab, and frequency and timepoint of swabs will also be fitted in separate models, to assess evidence for the presence of interactions.
- Models and reporting of results will be as per the primary analysis.

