**Bayesian analysis**

- Primary outcome main analysis will also be conducted in a Bayesian framework using ACCEPT analyses (5) reporting the probability that one treatment arm is more effective than another treatment arm based on a continuous range of efficacy thresholds.
- Models will be fitted as the primary analyses above.
- Sensitivity analysis to prior assumptions will be performed using non-informative, optimistic and sceptical priors (see appendix for details). The analysis will focus on non-informative

priors, with informative priors used for sensitivity analysis, unless there are model fitting issues with non-informative priors.

- Posterior probability curves will be created for each factor compared to SOC and between arms within a factor.
- The posterior probability of each arm truly being better than the comparator will be calculated for each factor arm compared to SOC and between arms within a factor.

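### SAP 4.6 lets the additional primary-outcome analyses, including the SAP's only firm comparison with standard of care, go unreported depending on the primary result

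*Protocol*

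**What the plan says.** The introduction to SAP section 4 sets the default: "All analyses will be included in the interim and final reports unless stated". Section 4.6 then makes two exceptions. Efficacy data are withheld from the interim report, which is sound. The second exception is "Analyses beyond the primary analysis may not be presented at final analysis, depending on results from primary analysis".

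The same section goes on to specify nine further analyses of the primary outcome under their own headings, mostly in firm terms:

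- Interaction models "will also be fitted in separate models, to assess evidence for the presence of interactions", with results reported in the same way as the primary analysis.
- Models of the change to the first and to the final swab, also stated as planned.
- Sensitivity analyses for time since antiseptic and for IV antibiotics.
- Three deviation analyses (censoring, multiple imputation, inverse-probability weighting), each triggered by a deviation rate above 15%.
- "Primary outcome main analysis will also be conducted in a Bayesian framework using ACCEPT analyses", with posterior curves and probabilities for each factor against SOC and between levels within a factor.
- Subgroup analyses, five maternal and nine neonatal.

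Protocol 4.10.4 says that the analysis will be frequentist and "Bayesian, enabling estimation of the probability that one arm is truly superior to another". It also plans estimates with 95% confidence intervals against control, exploratory interaction analyses and inverse-probability weighting. None of these depends on the primary result.

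**The concern.** A rule that lets pre-specified analyses be presented or withheld according to the primary result leaves the content of the report to be chosen after the data are seen. With no criterion in the SAP, a reader of the report cannot tell whether an absent analysis was dropped for a neutral reason or because of what it showed or might show. The rule names no direction, so it allows selective reporting after either kind of result.

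The SOC comparison is the most exposed. The trial hypothesis in the protocol's Executive Summary is a greater reduction than in controls, and the sample size section states power for contrasts with SOC. In SAP 4.6, however, the listed levels of the antiseptic and frequency effects do not include SOC, the reference is a single application of 1% CHG, and comparisons with SOC are only something that may be done. The Bayesian subsection is the one place where the SAP firmly plans inference against SOC on the primary outcome. If it can be left out, a final report could follow the SAP and give only descriptive SOC figures for the main endpoint. The trial is meant to select a regimen for a larger trial, so this matters.

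**Working it through.** **Passages side by side**

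| Analysis of the primary outcome | Commitment elsewhere | Effect of the 4.6 rule |
|---|---|---|
| Bayesian/ACCEPT, including SOC | Firm in protocol 4.10.4 and in SAP 4.6 | Presentation optional |
| Interactions | Exploratory but planned in protocol 4.10.4; firm in SAP 4.6 | Presentation optional |
| First/final swab | Firm in SAP 4.6 | Presentation optional |
| Time since antiseptic; IV antibiotics | Planned in SAP 4.6 | Presentation optional |
| Deviation analyses | Objective 15% trigger in SAP 4.6; weighting unconditional in protocol 4.10.4 | A second, undefined trigger is added |
| Subgroups | Planned in SAP 4.6 | Presentation optional |
| Frequentist comparison with SOC | Planned in protocol 4.10.4; optional in SAP 4.6 | Already optional |

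The only two inferential routes to SOC on the primary outcome are the Bayesian row and the last row. The SAP leaves both open.

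**Power, as context**

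Inputs, from SAP 2.4: "147 individuals randomized to 7 treatment groups, 21 participants per group". Pooling over the other factor gives 2 × 21 = 42 per antiseptic, 3 × 21 = 63 per frequency and 21 in SOC. Design alphas are 0.012 (antiseptic contrasts), 0.05 (frequency) and 0.025 (frequency v SOC). SAP section 4 plans no multiplicity adjustment at analysis, so 0.05 is shown as well.

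Formula, with d in SD units: power = Φ(d / √(1/n1 + 1/n2) − z(1−α/2)).

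The plan's own figures first. For example, the plan "provides 90% power to detect a difference of 0.82 standard deviations (SDs) between antiseptics":

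- √(2/42) = 0.218; 0.82/0.218 = 3.76; 3.76 − 2.51 = 1.25; power 89.4%.

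All eight stated figures reproduce to within 2 percentage points:

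| Contrast | n | Alpha | Power at the 90% effect | Power at the 80% effect |
|---|---|---|---|---|
| Antiseptics | 42 v 42 | 0.012 | 89.4% (0.82 SD) | 78.4% (0.72 SD) |
| Frequencies | 63 v 63 | 0.05 | 90.2% (0.58 SD) | 80.1% (0.50 SD) |
| Antiseptic v SOC | 42 v 21 | 0.012 | 89.7% (1.01 SD) | 78.3% (0.88 SD) |
| Frequency v SOC | 63 v 21 | 0.025 | 90.8% (0.90 SD) | 81.4% (0.79 SD) |

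The same formula at d = 0.5 SD:

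- Antiseptics: 0.5/0.218 = 2.29. Power is Φ(2.29 − 2.51) = 41% at 0.012 and Φ(2.29 − 1.96) = 63% at 0.05.
- Frequencies: 80% at 0.05, the plan's own value.
- Antiseptic v SOC: √(1/42 + 1/21) = 0.267; 0.5/0.267 = 1.87. Power is 26% at 0.012 and 46% at 0.05.
- Frequency v SOC: 40% at 0.025 and 51% at 0.05.
- Antiseptic × frequency contrast, 21 per cell: √(4/21) = 0.436; 0.5/0.436 = 1.15. Power is 21% at 0.05.

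Two factors that the documents do not quantify act in opposite directions. An assumed 10–30% loss of participants lowers antiseptic power at 0.05 to 59–48%. An assumed baseline correlation of 0.3–0.5, if the stated SD is unadjusted, raises it to 67–75%.

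**The case against.** The strongest reply is that the harm is already contained. SAP section 4 says that results will not be sorted into significant and non-significant and that 95% confidence intervals will be used. A reader might infer that the rule lets a null primary result close the question. The documents do not support that: no direction is named, and the SAP rules out a yes/no reading.

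A reader might also infer that everything beyond the primary analysis can be dropped. That is too wide. The log CFU summary table in 4.6 is firmly planned, skin score, temperature and adverse events have their own sections (4.8 to 4.10), and the species and component analyses have a separate rule in 4.11.

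Nor is it right that the primary comparisons generally miss a half-SD effect. Frequency has 80% power at 0.50 SD, and for antiseptics the team chose 0.72–0.82 SD as its target. Power does not depend on the reporting rule at all, and the protocol openly says that the trial is not powered for interactions.

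It can further be said that the rule concerns presentation rather than conduct, and that a Bayesian analysis with a difference prior of SD 20 would add little to an estimate and its interval.

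These limits stand and narrow the point, but they do not remove it. An analysis that is run and not shown is still selectively reported. For SOC, the SAP firmly plans no frequentist estimate that could stand in for the Bayesian one. Protocol 4.10.4 does plan such a comparison, but that makes the two texts inconsistent; it does not repair the SAP.

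**Conclusion.** The point holds for the additional primary-outcome analyses in SAP 4.6. Their presentation depends on the primary result without any criterion, against both the protocol and the subsections that specify them. Nine headed analyses are affected, three of which already have an objective trigger. The gravest consequence is that the SAP's only firm inferential comparison with SOC on the primary outcome becomes optional.

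This conclusion rests on the text and needs no power calculation. The figures only show that an antiseptic result near the null would leave half-SD differences open: power is about 41–63% on the pooled two-sample formula, assuming no interaction and no loss. An observed difference of zero would carry a 95% interval of about ±0.43 SD (1.96 × 0.218). Supporting analyses would then be informative. Reading the rule as covering the additional 4.6 analyses follows from its position; the SAP does not define its scope.

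**What to change.** Delete the sentence from SAP 4.6 before database lock. State instead that the pre-specified 4.6 analyses will be reported whatever the primary result, in a supplement where space requires, with the three deviation analyses reported when their 15% trigger is met. If some discretion must remain, fix a minimum list that is always reported: the Bayesian/ACCEPT analysis including the SOC comparisons, and the interaction analyses. If a listed analysis cannot be run, for example because a model fails to fit, the report should say so.

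The cost is one sentence in the SAP and a longer report. No new analysis has to be designed. More unadjusted results will be on view, but the SAP already says that interpretation will take multiple testing into account.
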